#### Data collection and analysis

Outcome and ecological momentary data will be assessed using online questionnaires programmed in the FACE self-help app. Data integrity is ensured through a variety of mechanisms, i.e. referential data rules, valid values, range checks, and consistency checks. In addition, data on the use of the modules are collected within the platform. All the data will be identified by a code that is not related to the participant’s identity. Servers are protected by high-end firewall systems and are located in data centres in the EU (Helsinki, Falkenstein) that comply with the GDPR and are ISO 27,001 certified. All the data will be handled confidentially and in addition to the technical administrators, only the researchers directly involved in the study have access to the data. Three audits and data monitoring will be performed by the person responsible for ethics and data security at the School of Social Work of the University of Applied Sciences and Arts Northwestern Switzerland.

#### Handling of missing data and dropout

Dropout is defined as participants who withdraw actively from the intervention after randomisation. All the other participants will receive an e-mail invitation to complete the post- and follow-up-questionnaires in any case. All dropout cases are part of the intent-to-treat sample, as they have been randomised and are included in the analyses. We will analyse the extent of missing data, explore the missing data patterns, and determine the type of missing data (Missing Completely at Random, Missing at Random, Not Missing at Random). Depending on the analysis, missing values will be replaced using multiple imputations. Sensitivity analyses will explore the impact of the imputation of missing values.

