### Statistical analyses

Analyses will be conducted according to the intention-to-treat paradigm. Additionally, we will conduct per-protocol analyses, including participants who complete baseline and post-intervention assessments and log into at least four modules defined as minimal therapeutic exposure. The significance level will be two-sided at *p* ≤ 0.05. To test the efficacy of the intervention in the intervention group compared to the control group, we will use linear mixed models. The differential effects of the SER and SSIP components will then be tested with interactions between the component and time. These analyses will model random slopes and intercepts for participants, test the fixed effects of the condition, as well as repeated assessments over time, using data from all participants. Linear mixed models have the advantage that they can account for missing values through maximum likelihood estimation [74]. Cohen’s d and f will be calculated as effect sizes. Furthermore, we will calculate Reliable Change Indexes [75].

Potential predictors and moderators of intervention outcome, such as gender or ACE severity will be analysed using multiple linear regressions. To analyse the mediation hypotheses and the longitudinal interplay of the variables, we will conduct path and structural equation analyses. Analyses will be conducted in SPSS, R and Mplus. There are no statistical stopping rules in this trial.

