The primary aim of this study is to assess the efficacy of the app in enhancing resilience and well-being as well as other outcome variables in emerging adults with ACE. Additionally, the results will offer insights into the differential impact of the SER and SSIP components on fostering resilience and well-being and secondary outcomes such as self-efficacy for managing emotions, problem-solving, or fear of negative evaluation. The FACE intervention study is embedded in a three-wave epidemiological study to investigate emotion regulation and social information processing as mechanisms that link ACE with psychosocial functioning in emerging adulthood [50]. The epidemiological study based on a random population sample is used to identify emerging adults with a history of ACE who then are invited to take part in the intervention. Thus, the sample of the intervention study may include participants who would not have sought help on their own and who may be less self-selective than samples in intervention studies with a passive recruitment strategy. Moreover, the longitudinal epidemiological data also offer a broad basis for identifying predictors and moderators of treatment outcomes, such as the type and severity of ACE or previous help-seeking.

In addition to the epidemiological data, the retrospective self-report questionnaires for evaluating the app are complemented with EMA data on affective states, social interactions and coping strategies before and after the intervention as well as between the two components. The EMA data can detect context-dependent associations between emotion regulation, social information processing and psychosocial functioning in daily life. It provides real-life data for the evaluation of the app that is less prone to memory bias and can provide ecologically more valid insights into the effects of the app. Thus, by drawing on the longitudinal epidemiological and the EMA data, the FACE study extends the existing knowledge on self- and emotion regulation and social information processing as mechanisms for fostering resilience in emerging adulthood.

Limitations of the study are that self-help interventions have high dropout rates and that the effect sizes are lower than in blended counselling interventions [79, 80]. Furthermore, all the data from the participants are self-reported and thus subject to different types of bias, notably social desirability bias and non-response bias.

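### As written, people who actively withdraw from the app get no invitation to the t2 and follow-up questionnaires, although they stay in the intention-to-treat sample

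*Protocol article*

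**What the plan says.** All of this comes from the protocol article.

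- *Handling of missing data and dropout* gives the definition: "Dropout is defined as participants who withdraw actively from the intervention after randomisation". The next sentence reads: "All the other participants will receive an e-mail invitation to complete the post- and follow-up-questionnaires in any case". The section then adds: "All dropout cases are part of the intent-to-treat sample, as they have been randomised and are included in the analyses".
- *Statistical analyses* sets the principle: "Analyses will be conducted according to the intention-to-treat paradigm". It relies on the mixed model for incomplete data: "Linear mixed models have the advantage that they can account for missing values through maximum likelihood estimation".
- *Handling of missing data and dropout* also provides for imputation, "Depending on the analysis, missing values will be replaced using multiple imputations", and for one check, "Sensitivity analyses will explore the impact of the imputation of missing values". It says the type of missingness will be determined, and it lists not missing at random among the types.
- *Primary and secondary outcomes* places t1 at 5 weeks and t2 at 11 weeks after the start, with follow-up 11 weeks after the app is finished. Reminders are planned after 2 and 4 weeks.
- *Discussion* names dropout as a general weakness of this type of intervention: "Limitations of the study are that self-help interventions have high dropout rates". No rate is given anywhere.

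**The concern.** Dropout is defined by leaving the intervention, but it decides who is asked for outcomes. An intention-to-treat analysis needs outcomes from people who stopped treatment as well as from those who continued. Keeping withdrawers in the analysis set does not supply those outcomes. Their t2 and follow-up values have to come from the model or from imputation.

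The loss is also unequal between the arms. Up to t2 the comparator is a waiting list with no app to leave, so the rule takes outcomes mainly from the active arm in the primary comparison of resilience and well-being. Under missing at random, withdrawers are in effect given the course of stayers with similar observed scores. If they did worse than those stayers, the comparison favours the app. Outcomes that were never requested cannot be recovered at the analysis stage.

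**Working it through.** **Who is invited, as written**

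| Participant | Dropout as defined? | Invited to t2 and follow-up? | Outcome data available |
|---|---|---|---|
| Uses the app throughout | No | Yes | t0, t1, t2, follow-up |
| Stops logging in, says nothing | No | Yes | All visits, if they respond |
| Actively withdraws after t1 | Yes | No | t0 and t1 |
| Actively withdraws before t1 | Yes | No | t0; the text does not say whether t1 is sent |

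The gap therefore concerns active withdrawers only. No other section of the article provides for collecting their outcomes.

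**The plan's own figures.** The article gives no withdrawal rate and no bias calculation to reproduce. Its repeated-measures sample sizes do reproduce. With noncentrality f² × N × m / (1 − r), m = 3 and r = 0.6, two groups and f = 0.25 give N = 24 (power 0.835). Three groups and f = 0.10 give N = 162 (power 0.801). This point does not dispute them.

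**Size of the possible bias**

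Inputs:
- w, the proportion of the active arm that actively withdraws without t2 data. This is an assumption.
- d_s, the t2 effect in stayers. It is assumed to be 0.40 SD.
- d_w, the t2 effect in withdrawers. It is assumed to be 0 or half of d_s (0.20 SD).
- Active-arm size: 250 × 2/3 ≈ 167, from the maximum sample and the 1:2 allocation in the article.

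Formulas:
- True intention-to-treat effect = (1 − w) × d_s + w × d_w.
- Estimate under missing at random ≈ d_s, when the observed scores carry little sign that withdrawers are doing worse.
- Overstatement = w × (d_s − d_w).

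| w | Active withdrawers of 167 | d_w | True effect | Estimate | Overstatement |
|---|---|---|---|---|---|
| 5% | about 8 | 0 | 0.95 × 0.40 = 0.38 | 0.40 | 0.02 (5%) |
| 10% | about 17 | 0.20 | 0.36 + 0.02 = 0.38 | 0.40 | 0.02 (5%) |
| 10% | about 17 | 0 | 0.90 × 0.40 = 0.36 | 0.40 | 0.04 (11%) |
| 20% | about 33 | 0.20 | 0.32 + 0.04 = 0.36 | 0.40 | 0.04 (11%) |
| 20% | about 33 | 0 | 0.80 × 0.40 = 0.32 | 0.40 | 0.08 (25%) |
| 30% | about 50 | 0 | 0.70 × 0.40 = 0.28 | 0.40 | 0.12 (43%) |

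Percentages are relative to the true effect. With 0.50 SD in stayers and no benefit in withdrawers, the overstatement is 0.05, 0.10 and 0.15 SD at 10%, 20% and 30%. It halves if withdrawers keep half the benefit. Where a late withdrawer's t1 score already shows a poorer course, the model uses it and the overstatement is smaller.

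**The case against.** The strongest reply is that the exclusion is inferred. No sentence says that withdrawers will not be contacted; it follows only from the contrast with the other participants. The article calls the whole trial an intervention study, so withdrawing from the intervention may be shorthand for leaving the trial, and then not e-mailing these people would be expected. A full protocol might draw the distinction. It is also ordinary for an analysis plan, rather than an article, to choose the method for data not missing at random. The article does list that mechanism.

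Part of this stands. The authors may have meant withdrawal from the study. But the definition is printed in terms of the intervention, and the invitation rule is built on it. Either reading requires the sentence to be changed or clarified. The absence of a named not-at-random method is not an error in itself. It matters here because the invitation rule creates the missing data, and because observed data cannot tell missing at random from not missing at random.

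Four stronger readings might be inferred, and the documents do not support them:
- *Anyone who stops using the app is lost.* Those who lapse without actively withdrawing are still invited.
- *Withdrawers have no data after baseline.* Those who leave after t1 have t1 data.
- *The planned sensitivity analysis only sets imputation against maximum likelihood.* The article does not say what it compares.
- *The bias is known to be large and in favour of the app.* The remark on high dropout is general and may cover more than active withdrawal. Nothing states why people withdraw. Leaving for lack of time, or because one feels better, could weaken or reverse the direction.

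**Conclusion.** The point holds for active withdrawers. As written, leaving the app ends invitations to t2 and follow-up without any withdrawal of consent to data collection. That conflicts with the stated intention-to-treat analysis, and up to t2 it affects essentially one arm.

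The documents do not fix the size of the consequence. If withdrawers benefit less than comparable stayers, the overstatement is about the withdrawal proportion times the difference in benefit. With 0.40 SD in stayers this runs from 0.02 SD (5% withdrawal with no benefit, or 10% with half the benefit) to 0.08 SD (20% with no benefit). The withdrawal rates, the stayers' effect and the reduced benefit are all assumptions. If few people actively withdraw, or if they do as well as comparable stayers, little is lost. The change is still worth making because it is cheap and the lost outcomes cannot be recovered.

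**What to change.** 1. Define two separate events: withdrawal from the app, and withdrawal of consent to further contact or data collection.
2. Invite every randomised participant who has not withdrawn that consent, in both arms, to t1, t2 and follow-up, with the reminders already planned. Use these data in the primary model. The questionnaires are programmed in the app, so check that someone who has left the intervention can still open them.
3. Report the number and timing of active withdrawals by arm.
4. Add one sensitivity analysis that departs from missing at random for outcomes still missing, for example delta-adjusted imputation or reference-based imputation from the waiting-list course.

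The cost is a reworded sentence or two, a changed mailing list, a few more e-mails and one extra analysis. No more participants are needed. Recruitment was planned to end in July 2024. If data collection has already closed, steps 3 and 4 remain possible, and the report should state whether withdrawers were in fact invited.

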## Discussion

Adverse childhood experiences are common, cause substantial personal suffering and are a well-established transdiagnostic risk factor for various mental and physical health conditions throughout life. While primary prevention for reducing ACE is crucial, selective prevention aims to mitigate the harmful short- and long-term consequences of ACE. The guided FACE app for fostering resilience and well-being among emerging adults with a history of ACE targets self- and emotion regulation as well as social skills and biased social information processing. Thus, it targets risk processes instead of treating later symptoms of a disorder. Furthermore, it is delivered at an opportune time in life when emerging adults start to take control of their own lives and become independent of their parents. This stage in life offers a window of opportunity for recovery, but also holds a risk for the consolidation of problems and deterioration of trajectories. Thus, the FACE app has high potential for preventing and mitigating the adverse effects of ACE and thus reducing the need for more intensive psychotherapy for chronic dysfunctions later in life.

The FACE app was developed in an iterative co-design with emerging adults and delivers the interventions in an easy-to-use and low-threshold framework adapted for the target group. It offers psychoeducative materials and exercises in various formats (text, audio, video) on ACE and their impact and features a variety of interactive tools for use in everyday life. Additionally, participants receive one short personal feedback message a week to encourage the engagement with the app.

The primary aim of this study is to assess the efficacy of the app in enhancing resilience and well-being as well as other outcome variables in emerging adults with ACE. Additionally, the results will offer insights into the differential impact of the SER and SSIP components on fostering resilience and well-being and secondary outcomes such as self-efficacy for managing emotions, problem-solving, or fear of negative evaluation. The FACE intervention study is embedded in a three-wave epidemiological study to investigate emotion regulation and social information processing as mechanisms that link ACE with psychosocial functioning in emerging adulthood [50]. The epidemiological study based on a random population sample is used to identify emerging adults with a history of ACE who then are invited to take part in the intervention. Thus, the sample of the intervention study may include participants who would not have sought help on their own and who may be less self-selective than samples in intervention studies with a passive recruitment strategy. Moreover, the longitudinal epidemiological data also offer a broad basis for identifying predictors and moderators of treatment outcomes, such as the type and severity of ACE or previous help-seeking.

In addition to the epidemiological data, the retrospective self-report questionnaires for evaluating the app are complemented with EMA data on affective states, social interactions and coping strategies before and after the intervention as well as between the two components. The EMA data can detect context-dependent associations between emotion regulation, social information processing and psychosocial functioning in daily life. It provides real-life data for the evaluation of the app that is less prone to memory bias and can provide ecologically more valid insights into the effects of the app. Thus, by drawing on the longitudinal epidemiological and the EMA data, the FACE study extends the existing knowledge on self- and emotion regulation and social information processing as mechanisms for fostering resilience in emerging adulthood.

Limitations of the study are that self-help interventions have high dropout rates and that the effect sizes are lower than in blended counselling interventions [79, 80]. Furthermore, all the data from the participants are self-reported and thus subject to different types of bias, notably social desirability bias and non-response bias.

The findings from this study will inform the development of other interventions for coping with a history of ACE. It will also suggest improvements to the FACE app and evaluate its potential for large scale deployment as a low-threshold intervention to support emerging adults with a history of ACE in the transition to adulthood. This is particularly relevant in the context of current challenges with access to mental health services for emerging adults in Switzerland and elsewhere. A broadly accessible, and low-threshold self-help app such as the FACE app holds promise in complementing existing mental health support offers, potentially reducing the personal and societal harm associated with ACE.

## Data Availability

No datasets were generated or analysed during the current study.

## Abbreviations

ACE: Adverse childhood experiences
E-health: Digital self-help interventions
EMA: Ecological momentary assessments
M-health (/Mobile-health): Interventions delivered on smartphones (subcategory of E-health)
PWA: Progressive web app
SER: Self- and emotion regulation
SSIP: Social skills and social information processing
